## Abstract

**Background: **Neonatal infection is the third largest cause of death in children under five worldwide.  Nutritional immunity is the process by which the host innate immune system limits nutrient availability to invading organisms. Iron is an essential micronutrient for both microbial pathogens and their mammalian hosts. Changes in iron availability and distribution have significant effects on pathogen virulence and on the immune response to infection. Our previously published data shows that, during the first 24 hours of life, full-term neonates have reduced overall serum iron. Transferrin saturation decreases rapidly from 45% in cord blood to ~20% by six hours post-delivery.

**Methods: **To study neonatal nutritional immunity and its role in neonatal susceptibility to infection, we will conduct an observational study on 300 full-term normal birth weight (FTB+NBW), 50 preterm normal birth weight (PTB+NBW), 50 preterm low birth weight (PTB+LBW) and 50 full-term low birth weight (FTB+LBW), vaginally-delivered neonates born at Kanifing General Hospital, The Gambia. We will characterize and quantify iron-related nutritional immunity during the early neonatal period and use
*ex vivo* sentinel bacterial growth assays to assess how differences in serum iron affect bacterial growth. Blood samples will be collected from the umbilical cord (arterial and venous) and at serial time points from the neonates over the first week of life.

**Discussion: **Currently, little is known about nutritional immunity in neonates. In this study, we will increase understanding of how nutritional immunity may protect neonates from infection during the first critical days of life by limiting the pathogenicity and virulence of neonatal sepsis causing organisms by reducing the availability of iron. Additionally, we will investigate the hypothesis that this protective mechanism may not be activated in preterm and low birth weight neonates, potentially putting these babies at an enhanced risk of neonatal infection.

**Trial registration: **clinicaltrials.gov (
NCT03353051) 27/11/2017

## Abbreviations

PTB = Preterm birth

FTB = Fullterm birth

LBW = Low birthweight

NBW = Normal birthweight

WHO = World Health Organisation

TSAT = Transferrin saturation

MDG = Millennium development goal

GBS = Group B
*Streptococci*

EONS = Early onset neonatal sepsis

YICSS = Young Infants Clinical Signs Studies

KGH = Kanifing General Hospital

MRCG = Medical Research Council Unit The Gambia at LSHTM

KMC = Kanifing Municipal Council

UIBC = Unbound iron-binding capacity

IL6 = Interleukin 6

IL22 = Interleukin 22

sTfR = Soluble transferrin receptor

CRP = C-reactive protein

AGP = Alpha 1-acid glycoprotein

HIV = Human immunodeficiency virus

TB = Tuberculosis

EDTA = Ethylenediaminetetraacetic acid

V1 = Venous bleed 1

V2 = Venous bleed 2

IM = Intramuscular

ELISA = Enzyme-linked immunosorbent assay

ID = Identification

CRF = Case report form

eCRF = Electronic case report form

ANOVA = Analysis of variance

IDE = Integrated development environment

CyTOF = Cytometry by time of flight

STAT3 = Signal transducer and activator of transcription 3

TLR = Toll-like receptor

SOP = Standard operating procedure

OD = Optical density

WBC = White blood cell

LPS = Lipopolysaccharide

## Introduction

### Neonatal infections – challenges in low-income settings

Neonatal infection is the third largest cause of death in children under-five worldwide and is an ongoing major global public health challenge (Sustainable Development Goal 3.2)
^1^. Between 1990 and 2016 maternal and under-five child mortality has decreased by half
^2^. However, the proportion of neonatal deaths among under-five deaths increased from 37% (1990) to 44% (2013)
^3,
4^. Today, approximately 2.8 million children die annually during the neonatal period – the first 28 days of life. Of these, 73% die within the first six days of life
^3^. An increasing proportion of child deaths are in sub-Saharan Africa
^5^, with 60–80% of newborn deaths occurring in low birthweight (LBW) neonates (<2500g at birth)
^6^. 95% of all LBW neonates are born in low-income countries
^7^. However, the situation is likely to be worse than documented, as neonatal deaths in developing countries are commonly under reported and the records commonly contain errors
^8,
9^. It is estimated that about one third of deaths in the first month of life, are caused by infections including bacterial sepsis, meningitis, pneumonia, neonatal tetanus, and diarrhoea
^10^.

Evidence is lacking on the aetiology of neonatal infections in developing countries, especially from community settings
^11,
12^. However, the limited data suggests that
*Klebsiella* species,
*Escherichia coli,* and
*Staphylococcus aureus* are common causes of early onset sepsis (EONS)
^13–
15^. The available antibiotic susceptibility data suggests that pathogens associated with neonatal sepsis in developing countries are often resistant to WHO-recommended empiric antibiotics
^13,
16^. Antibiotic resistance has emerged with potency over the last few decades due to a multitude of complex reasons. Antibiotic overuse, inappropriate prescribing, inadequate diagnostics, extensive agricultural use, availability of few new antibiotics, and the ease of transportation of resistant bacteria are among the factors contributing to the rise. Equally, bacteria have the ability to rapidly mutate (with or without drug selection pressure) and horizontally transfer genetic material between species (i.e. non-human pathogens) of bacteria
^17,
18^. Neonates are particularly at risk from antibiotic resistant organisms because they generally succumb before alternative antibiotic regimes can be tried.

Diagnosis of neonatal sepsis with high specificity remains challenging in developing countries. A widely used tool developed by the World Health Organization Young Infants Clinical Signs Studies (YICSS), which includes seven clinical signs to aid diagnosis, has only a 85% sensitivity and 75% specificity for severe bacterial infection during the first week of life
^19^. Microbiological identification of a pathogen isolated from blood cultures often has higher specificity, but microbiological laboratory facilities are frequently lacking in low-income settings
^19^. With this all in mind, there is an immediate need to improve our understanding of neonatal blood-borne infections and develop novel therapies that could enhance immunological protection possibly via boosting innate immune mechanisms.

### Nutritional immunity

Iron is critical for the human host and most pathogens. Iron is one of the most important factors in the host-pathogen battle for resources. Bacteria and other pathogens have evolved a wide variety of mechanisms to acquire iron from the nutrient rich host (e.g. siderophores and iron specific channels)
^20^ to aid growth and virulence, with a number of iron acquisition genes concentrated on high pathogenicity islands
^21^.

Nutritional immunity describes the normal physiological innate processes used by the host to combat infection by limiting nutrient availability. Key among these processes is the ability to rapidly decrease the circulating concentration of iron (and other transition metals) in response to an infection
^22^. The hypoferremia of inflammation is mediated by the hormone, hepcidin. Research completed in 2000–2001 by three independent research groups led to the discovery of the hepcidin hormone, and the important function it plays in many aspects of iron metabolism
^23–
25^. Hepcidin is now understood to be the master regulator of iron homeostasis. Unlike any other micronutrient, iron is regulated by a hormone that responds to both infection and nutritional status. The host inflammatory mediators, IL6
^26^, IL22
^27^ and Type 1 interferon
^28^, have been found to increase transcription of hepcidin through several Toll-like receptor (TLR) ligands
^29^ and STAT3 signalling
^30,
31^ resulting in decreased systemic iron concentrations in the circulation. This multifaceted mechanism limits nutrient availability to extracellular invading microorganisms
^32^. The system is well documented in mouse models
^33–
35^, but less so in human studies. However, it is clear that humans with excessive levels of serum iron (e.g. due to hemochromatosis) are predisposed to infection with iron-dependent species of bacteria
^36,
37^.

### Neonatal hypoferremia

Although iron metabolism in adults and older children is well studied, the kinetics of iron handling in the early neonatal period, a time of intense physiological change, are poorly understood
^38^. Childbirth results in a neonate moving from a semi-allogeneic, protected and nearly sterile environment to one that is abundant in a diverse array of microbes. The delivery process is the initial focal point for the mass bacterial colonisation of the skin and gastrointestinal tract of the neonate
^39,
40^. Neonates are known to have very low levels of immunological memory and possess an immature immune system
^41^. Post-natal iron metabolism in neonates is controlled by an array of different signals, such as hypoxia, erythropoietic drive, maternal and foetal iron stores
^42^. A number of studies have investigated serum iron, transferrin saturation (TSAT), ferritin and haemoglobin levels at the time of birth using cord blood as a proxy for early neonatal blood
^43,
44^. A recent prospective study showed neonates born preterm compared to early-term had higher serum iron concentrations in umbilical blood, which was inversely correlated with levels of serum hepcidin
^45^. A similar study has also shown that small-for-gestational-age neonates and neonates born by elective caesarean have lower levels of hepcidin
^44^. Previous work has shown that serum iron and TSAT decreases between birth and the first 6–12 hours post-partum in full term, healthy vaginally delivered newborns
^46,
47^.

The study described here will shed light on the effects of prematurity and birthweight on body iron distribution immediately after birth and during the first week of life. Free ferric and ferrous iron (i.e. transferrin bound iron), haem-based iron molecules and their chaperone proteins (haem-hemopexin and haemoglobin-haptoglobin) will also be investigated.

### Study objectives

The primary study objective is to characterize in detail how full term, preterm and low birthweight neonates modulate serum iron in the first 24 hours of life. We hypothesize that premature and/or low birthweight babies have a defect in their ability to sequester iron at 6–24 hours after birth in comparison to full term neonates with normal birthweight.

The secondary objectives are:

I. Characterise how iron metabolism, handling and recycling differs between full term, preterm and low birthweight neonates at birth and during the first 24 hours of life.II. Describe iron metabolism, handling and recycling in full term neonates at birth and during the first 7 days of life.III. Determine if sera from preterm and low birthweight neonates supports a greater level of
*ex-vivo* growth of microorganisms that are common causes of neonatal sepsis in Africa and The Gambia (
*Staphylococcus aureus*,
*Klebsiella pneumoniae*,
*Escherichia coli*, Group B
*Streptococcus*,
*Streptococcus pneumoniae* and
*Salmonella enterica* serovar Typhimurium (
*S.* Typhimurium hereafter)) in comparison to sera from full term, normal birthweight neonates.IV. Characterize frequencies and functionality of neutrophils, monocytes, dendritic cells, NK cells, B cells and T cells (D8 and CD4) in cord blood from full term, premature and low birthweight neonates.

## Protocol

### Study site

Study participants will be recruited from Kanifing General Hospital (formally Serrekunda General Hospital), in the Kanifing region of The Gambia, West Africa. Serrekunda is a large town, forming a peri-urban area with a population of around 340,000, and is 13km to the southwest of the capital, Banjul. Serrekunda was originally made up of nine villages that have merged into a sprawling urban area. Annually, Kanifing General Hospital (KGH) provides antenatal care to 500–700 pregnant mothers. Mothers receiving antenatal care at other local healthcare facilities increase the total number of births at the hospital to 3500–4500 per year. The percentage of these that are live, low birthweight neonates (<2.5kg) is approximately 10%. Specimen samples will be subjected to primary processing on-site at KGH, followed by transport to Medical Research Council Unit The Gambia at LSHTM (MRCG) for storage and analysis.

### Participants

In total, 450 healthy newly born neonates will be identified during delivery at the Kanifing General Hospital Maternity Ward (
Figure 1) starting in July 2017. Pregnant mothers must be over the age of eighteen years. After informed consent is obtained, neonates who meet the inclusion criteria will be enrolled into the study. For inclusion in the study, neonates must be healthy, medically stable, greater than 32 weeks gestational age and weigh more than 2000g. To be considered preterm (PTB) the neonates will be < 37 weeks gestational age (assessed by New Ballard Score
^48^) and ≥ 32 weeks gestational age. All neonates with a gestational age ≥37 weeks will be considered full term (FTB). To be considered low birthweight (LBW) the neonates will weigh < 2500g. All neonates weighing ≥ 2500 g will be considered normal birthweight (NBW).

**Figure 1. f1:**
[figure not shown]
Main study flow chart of all study procedures and exclusion criteria. Group A will contain neonates characterised by preterm birth and low birthweight (PTB+LBW); Group B will contain neonates characterised by preterm birth and normal birthweight (PTB+NBW); Group C will contain neonates characterised by full term birth and low birthweight (FTB+LBW); Groups D1, D2 and D3 will all contain babies characterised by full term birth and normal birthweight (FTB+NBW). In this study, preterm is defined <37 weeks gestation and low birthweight is <2500g. Exclusion criteria (
**α**): Father refused, mother refused, family/escort refused, communication not possible or mother with severe disabilities. Exclusion criteria (
**β**): Antibiotics or antimalarials given before delivery (<24 hours), referred to tertiary level health facility, absconded, known HIV-positive, severe pre-eclampsia, receiving TB treatment, antepartum haemorrhage, recent blood transfusion (within the last month), no foetal heartbeat, mother <18 years, refusal, recruited to another study and emergency caesarean section. Exclusion criteria (
**γ**): Recruited to another study on-site, refusal, blood transfusion given in labour, antibiotics or antimalarials given during labour, neonate requires resuscitation (1 min APGAR), neonatal weight <2000g, neonate born breech, neonate born via vacuum delivery, neonate born caesarean section, foetal stillbirth, macerated stillbirth and major congenital malformations. Exclusion criteria (
**δ**): Failed cord blood collection (serum tubes), failed cord blood collection (EDTA), cord blood processed >6 hours, neonate requires resuscitation (10 min APGAR), absconded and route 2B refusal. Exclusion criteria (
**ε**): Mother birth check refusal, father birth check refusal, family escort birth check refusal, mother <18 years, recruited to another study on-site, antibiotics or antimalarials given to mother before delivery (<24 hours), neonate has had surgery, neonates sibling twin was recruited, neonate given antibiotics (other than tetracycline eye ointment), neonate given iron supplementation, neonatal sickness (tone, activity, feeding, heart rate, respiratory rate, abnormal anterior fontanelle), neonatal temperature (<36.5°C or >37.5°C), major congenital malformations (neonate), New Ballard Score (<32 weeks), failed V1 (serum), failed V1 (EDTA), failed V1 (both EDTA and serum), mother V1 bleed refusal, father V1 bleed refusal, and family/escort V1 bleed refusal. Exclusion criteria (
**ζ**): neonatal sickness (tone, activity, feeding, heart rate, respiratory rate, abnormal anterior fontanelle), neonatal temperature (<36.5°C or >37.5°C), neonate has had surgery, neonate given antibiotics (other than tetracycline eye ointment), neonate given iron supplementation, failed V2 bleed, Mother community/V2 bleed refusal, father community/V2 bleed refusal, and family community/V2 bleed refusal.

The study groups are:

Group A (PTB+LBW): Neonates who are both preterm and low birthweight.

Group B (PTB+NBW): Neonates who are preterm and normal birthweight.

Group C (FTB+LBW): Neonates who are full term but low birthweight.

Group D (FTB+NBW): Neonates who are full term and normal birthweight.

In addition to the main study, 300 FTB neonates of the 450 neonates will also be included into a sub-study, which aims to describe serum iron markers in full term babies (Group D, FTB+NBW only) over the first week of life.

### Study design

This is a proof-of-concept, observational cohort study (Groups A, B, C and D) with an embedded short prospective cohort study (Group D divided into D1, D2 and D3).

### Entry evaluation

***Consent and enrolment.*** There are two routes into the study enrolment (
Figure 2). Pregnant mothers who are receiving antenatal care on-site at KGH, will be approached at an antenatal visit and voluntarily sensitised to the study requirements and protocol (Route 1). Pregnant women, who are sensitised will not be required at that point to give written or verbal consent. This group will be provided with study information sheets and encouraged to discuss study participation with their family. When the pregnant woman returns to KGH Maternity Ward to deliver (some mothers will choose to deliver at other healthcare facilities), she will be asked to read the full study information sheet (or have it read to her by a study nurse if she is not literate) and provide formal written consent to the study involvement for their neonate (see Extended data
^49–
51^).

**Figure 2. f2:**
[figure not shown]
NeoInnate Study enrolment route and blood draw design. Group A contains neonates characterised by preterm birth and low birthweight (PTB+LBW); Group B contains neonates characterised by preterm birth and normal birthweight (PTB+NBW); Group C contains neonates characterised by full term birth and low birthweight (FTB+LBW); Groups D1, D2 and D3 all contain babies characterised by full term birth and normal birthweight (FTB+NBW).

Route 2 will provide an alternative route of enrolment for pregnant mothers, that would like their neonate to be part of the study but have been receiving antenatal care at another facility before delivering at KGH maternity ward. In route 2, healthy, pregnant women will enter the KGH ward to deliver and will be approached to provide written formal consent to umbilical cord blood collection and storage only. No testing or laboratory processes will be conducted on their sample, until full study consent is gained post-delivery. The cord blood sample will be stored at 4
^o^C (within the maternity ward), until the mother’s pain and discomfort subside Mothers will be approached 2-6 hours post-delivery on a one-to-one basis by our research clinician. The research clinician will independently verify if the mother displays normal psychological function and is not under distress before the consenting process begins. At this point, the mother and/or father will be invited to provide written formal consent on full study enrolment. If, at this point, mother and/or father refuse full study consent post-delivery, the previously collected personal information and umbilical cord sample will be safely discarded. Good clinical practise will be followed at all times.

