### Delivery procedures, post-delivery screening and umbilical cord blood collection

***Delivery procedures and screening.*** Study nurses will assist clinical KGH maternity ward staff in the delivery process and collect data via electronic case report form (eCRF) on their designated study tablets. Neonates will be excluded at the delivery stage of the study for the following reasons: major congenital malformations (not including polydactylism), blood transfusions given to mother or neonate, severe birth asphyxia (requiring resuscitation), neonates born via breech, vacuum or via caesarean section, or a birthweight <2000g. After the delivery stage of the study protocol, neonates can be excluded from the study following the detection of infection or illness (information gained from full blood count analysis or review of systems). Neonates will also be removed from the study protocol, if medication is given (not including intramuscular vitamin K, tetracycline eye ointment or any immunisations). All medication that is given to mothers and neonates will be recorded. Mothers will be able to refuse study participation at any stage. Mothers that deliver multiple newborns will only be invited to consent and enrol one of their neonates into the study.

***Umbilical cord blood collection.*** Once the neonate is fully delivered, one-minute delayed cord clamping will be used (following World Health Organisation (WHO) policy
^52^). During the one-minute delay, the one-minute APGAR score will be conducted. If the neonate requires resuscitation, the neonate will be excluded from the study. After the umbilical cord has been removed and cleaned, a trained study nurse will identify the umbilical arteries and the umbilical vein. Blood will be collected from both. The tubes will be placed in the cool box for 1–6 hours before transfer to the study laboratory for primary processing. If the mother is enrolled by route 2, the mother will be asked to provide written consent to full study recruitment before the sample is sent for primary laboratory processing. The time between the collection and the processing of blood samples will be recorded and analysed.

### Hospital assessment and 1
^st^ venous blood draw

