### Laboratory evaluations

***Blood samples.*** The processing of samples will be conducted 1-6 hours after collection to allow serum samples to coagulate and to allow mothers admitted via route 2 to give written consent. On arrival to the laboratory, whole blood samples in 4.5ml Sarstedt S-Monovette K3E (SARSTEDT AG & Co. KG, Germany) will be inverted five times and assessed for a full haematology panel using a Medonic M20M GP (Boule Diagnostics, Spanga, Sweden). The remaining whole blood sample will be aliquoted into 2ml Sarstedt micro tubes (SARSTEDT AG & Co. KG, Germany) and frozen at -20°C. Glucose-6-phosphate dehydrogenase deficiency testing (R&D Diagnostics Limited, Papagos, Greece) and sickle trait will be conducted at the end of the recruitment period of the study.

The Sarstedt S-Monovette Serum-Gel blood collection tube (SARSTEDT AG & Co. KG, Germany) will be centrifuged at 3500rpm for 10 mins using an Eppendorf Centrifuge 5702 (Eppendorf, Germany). Serum will be aliquoted into 2ml Sarstedt micro tubes (SARSTEDT AG & Co. KG, Germany), boxed and labelled before being stored at -20°C until after the recruitment period. The laboratory analysis of all serum samples will be conducted as one batch. All serum samples collected will be assessed by ELISA for the following: IL6, IL22, free haem, hepcidin, hemopexin, lipocalin-2, lactoferrin, and foetal haemoglobin. DRG Hepcidin 25 (bioactive) HS ELISA (EIA-5782) (dynamic range: 0.135 - 81 ng/mL), made by DRG Instruments GmbH, Germany, will be used to measure serum hepcidin. Additionally, serum ferritin, serum iron, UIBC, soluble transferrin receptor (sTfR), transferrin, C-reactive protein (CRP), haptoglobin, and alpha 1-acid glycoprotein (AGP) will be assessed using a fully automated biochemistry analyser (Cobas Integra 400 plus). Furthermore, umbilical WBC will be processed and analysed for exploratory secondary analysis 4.

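### The Route 2 consent window and the cool-box holding time both run up to the 6 h point at which late cord processing excludes the neonate, with no slack between them

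*Protocol article*

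**What the plan says.** Four places in the protocol article set the timing.

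- **Entry evaluation, Route 2 text (after Figure 2).** "Mothers will be approached 2-6 hours post-delivery on a one-to-one basis by our research clinician". Before that conversation can start, "The research clinician will independently verify if the mother displays normal psychological function and is not under distress before the consenting process begins". Until consent is given, the cord sample waits: "No testing or laboratory processes will be conducted on their sample, until full study consent is gained post-delivery".
- **Delivery procedures, post-delivery screening and umbilical cord blood collection.** For all neonates, "The tubes will be placed in the cool box for 1–6 hours before transfer to the study laboratory for primary processing". For Route 2, written consent must come before the sample is sent. The interval from collection to processing is recorded and analysed.
- **Laboratory evaluations.** "The processing of samples will be conducted 1-6 hours after collection", partly "to allow mothers admitted via route 2 to give written consent".
- **Figure 1 legend, exclusion criteria δ.** One reason for exclusion is "cord blood processed >6 hours".

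On the size of Route 2, Study site says that the hospital "provides antenatal care to 500–700 pregnant mothers" each year, against 3500–4500 births in total.

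**The concern.** Cord blood is taken just after delivery, so the consent clock and the processing clock start within minutes of each other. Both have 6 h as their upper limit, but they govern successive steps: consent must be finished, and the tube moved, before processing can take place. A mother approached late in the permitted window meets the consent rule and still leads to an exclusion. The same holds on either route for a tube held for the full permitted time and only then transferred.

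The consequence is large for what is at fault. The primary hypothesis concerns TSAT and serum iron at 6–24 h, measured in the first venous draw (V1). For that analysis the cord value is the adjustment covariate, and Statistical analysis also plans an unadjusted comparison that does not need it. Criteria δ nevertheless remove the whole neonate, at a stage listed before the one that contains V1. Sample size and power already foresees possible shortfalls in Groups A and B, so avoidable losses there would cost precision.

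**Working it through.** The plan gives no figure of its own on this point, so there is none to reproduce. The check compares the time limits and sizes the affected route.

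**1. Timing.** Let *a* be the time of approach after delivery and *L* the time needed for the check on the mother, consent, transfer and the start of processing. Collection follows delivery by minutes, so time to processing is approximately *a* + *L*. The limit is met only if *a* + *L* ≤ 6 h, that is, *a* ≤ 6 − *L*. The plan permits *a* up to 6 h. Any *L* of more than a few minutes leaves a part of the permitted window that cannot meet the limit. For the cool box, holding up to 6 h plus any transfer time gives more than 6 h.

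**2. Share of births under Route 2.** Route 1 comes from on-site antenatal mothers (500–700 a year); Route 2 is the remainder of 3500–4500 births.

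- Lowest: (3500 − 700)/3500 = 80%
- Highest: (4500 − 500)/4500 = 89%

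This treats every on-site antenatal mother as delivering on site. Entry evaluation says that some go elsewhere, which would raise the share. It is a share of hospital births; the share of enrolled neonates is not given.

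**3. Illustration of loss.** The documents give neither *L* nor the distribution of approach times. Assume approaches uniform over the 4 h from 2 h to 6 h. The part of Route 2 over the limit is then *L*/4.

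| Assumed *L* | Latest workable approach | Share of Route 2 over the limit | Share of all births (× 0.80 to 0.889) |
|---|---|---|---|
| 0.25 h | 5.75 h | 0.25/4 = 6.25% | 5.0–5.6% |
| 0.5 h | 5.5 h | 0.5/4 = 12.5% | 10.0–11.1% |

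If most approaches come early, the loss is smaller.

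**4. What the exclusion removes.** The Figure 1 legend lists late cord processing under δ and failed V1 under the next set, ε. V1 follows the hospital health assessment at 6–24 h. On that sequence a neonate excluded at δ has not been bled. The New Ballard Score is also done at that assessment, so the neonate has not been assigned to Groups A–D.

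**5. Existing safeguards.** Statistical analysis will consider imputation if more than 5% of data are missing, and sensitivity analyses if loss to follow-up differs between groups. A neonate excluded at δ counts as neither. Recording the collection-to-processing interval does not bring it back.

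**6. Why numbers matter in Groups A and B.** In Sample size and power, the difference detectable with 80% power rises from about 4% to 5.8% for TSAT, and from 2.5 to 3.3 μmol/L for serum iron, when Groups A and B fall from 50 to 25 each.

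**The case against.** The overlap was intended. Laboratory evaluations says that the processing window is there partly to accommodate Route 2 consent, and the cool-box period is probably the same window described again. Mothers approached with time to spare fit, and nothing says that approaches are usually late. This stands: the limits share an upper end without slack, and they are not incompatible throughout.

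Cord blood is also more than a covariate. Secondary objectives I and II start at birth, objective III compares growth in cord and V1 serum, and objective IV rests wholly on cord cells. Requiring a usable cord sample is a defensible choice, and imputing cord iron restores none of those data. This stands too, and limits what the fix can achieve. It does not explain why the V1 comparison should lose the neonate.

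Groups are recruited to targets, so an exclusion can be replaced by a later birth. That is partly right, but the plan names time and budget among its constraints.

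A reader might go on to infer three stronger points that the documents do not support:

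- **Heavy loss.** Lags of 1 or 2 h would give 25% or 50% of Route 2 under the same formula. Study site places primary processing at the hospital itself, so nothing supports delays of that length.
- **Collected primary-outcome samples thrown away.** On the listed sequence V1 has not yet been drawn. It is forgone.
- **Selection bias between groups.** The release of Route 2 mothers for consent depends on recovery from pain and discomfort, so a link with a difficult delivery is conceivable. But the plan already excludes caesarean, vacuum and breech births, resuscitation, severe pre-eclampsia and antepartum haemorrhage, and no text links consent time to prematurity, birthweight or V1 iron.

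**Conclusion.** The point holds in a limited form. A neonate handled within the stated consent or holding times, at their late end, can be excluded for late cord processing, and its V1 sample is then never taken. Route 2, where consent timing adds to the problem, covers about 80–89% of hospital births.

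The number lost is unknown. The range of about 6–12.5% of Route 2 rests on two assumptions, uniform approach times and 15–30 minutes for the remaining steps, and is an illustration only. It also takes the δ limit to run from collection, as the window in Laboratory evaluations does. The supported consequence is avoidable loss of primary-outcome data, most costly in Groups A and B. Differential loss across Groups A–D remains possible but not shown.

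**What to change.** 1. **Reconcile the timing** in the Route 2 text, the cord blood collection section, Laboratory evaluations and criteria δ, so that the latest permitted consent and holding times leave room for transfer and processing within the limit. State the event from which each clock runs.
2. **Treat cord blood processed late as a missing cord value**, not as a reason to exclude a consented neonate. Keep the neonate, take V1 and include it in the unadjusted comparison.
3. **Impute the cord covariate in the adjusted primary model**, within the imputation that Statistical analysis already contemplates; late samples then count towards its missing-data rate. Add a complete-case sensitivity analysis.
4. **Report the number of late cord samples by enrolment route and by group**, so that differential loss can be seen.

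The cost is a wording change and one imputation model. The downside is that these neonates have an imputed baseline and contribute nothing to the cord-based secondary objectives, such as the cord growth assays and cord cells.
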